## Abstract

**Background:**

Sickle cell disease (SCD) is a chronic inherited blood disorder that disproportionately affects African Americans. Managing SCD is complex, often requiring coordination of care among multiple health care professionals. These care challenges result in fragmented service delivery and poor health outcomes. Integrating community health workers (CHWs) into patient-centered coordinated care may enhance disease management and patient satisfaction with the care received.

**Objective:**

The proposed study aims to test the feasibility and acceptability of a CHW-integrated model for SCD management.

**Methods:**

This protocol is for a multimethod study to evaluate the feasibility of an integrated CHW intervention. The intervention includes CHW-led patient education and care coordination. Adults with SCD (aged 18‐45 years) will be recruited from the Augusta University Sickle Cell Center’s satellite clinic in Albany, Georgia. Quantitative outcomes include self-care behaviors and patient satisfaction. Qualitative data from semistructured interviews will be used to assess the acceptability of the intervention.

**Results:**

The proposed study will provide preliminary data on the impact of a CHW-integrated model on care coordination and self-management among adults with SCD. As of March 2026, we have enrolled 16 participants.

**Conclusions:**

Despite national calls for improved care coordination and disease management in this population, few published protocols detail community-based, culturally aligned approaches that center on the lived experiences and structural barriers faced by adults with SCD. Our study addresses a gap in the literature by highlighting a theory-informed, multimethod study protocol for evaluating the feasibility, effectiveness, and acceptability of integrating CHWs into a patient-centered coordinated care model for adults with SCD. This protocol outlines a scalable, community-embedded strategy that may inform future clinical trials and implementation efforts.

## Introduction

Sickle cell disease (SCD) is an inherited hemoglobin disorder that affects 1 in 365 African Americans [1,2]. Disparities in receiving health care among African Americans and other racial/ethnic minority groups in the United States are well documented and are directly related to poor health outcomes associated with SCD. Individuals with SCD experience physical, psychological, and social comorbidities that impact effective disease management [3,4]. The challenges of providing care to this population with complex needs have led to fragmented care, poor patient experiences, and inadequate implementation of evidence-based SCD management [5,6]. In 2014, the National Heart, Lung, and Blood Institute released a report on “Evidence-Based Management of Sickle Cell Disease” [7], calling for strategies to improve disease management by patients and providers [8]. Patient-centered coordinated care (PCCC) is an evidence-based strategy that can potentially reduce care fragmentation and improve patient experiences. However, studies report deficiencies in care coordination and patient satisfaction among individuals with SCD [9,10]. These deficiencies contribute to the inability of African Americans with SCD to obtain consistent, preventive care, resulting in poorer physical and psychological health outcomes.

Georgia ranks among the top 3 states in the prevalence of SCD, affecting more than 10,000 individuals, including a significant adult population, across nearly every county [11]. Access to specialized care constitutes a significant barrier for these individuals, as data from the Sickle Cell Data Collection program reveal that 10% of babies born with SCD between 2004 and 2016 lived more than 1 hour away from the nearest specialty care center, a situation that contributes to delays in treatment and increased health care use that can persist into adulthood [11]. Many adults with SCD experience challenges related to treatment adherence and health care access, which underscores the urgent need for community-based interventions aimed at enhancing support for this population. To address these barriers, the Georgia Senate Study Committee on Sickle Cell Disease recommended expanding community-based solutions, such as leveraging Federally Qualified Health Centers, mobile health units, and telemedicine—approaches that align with the integration of community health workers (CHWs) to support disease management [12].

A community-based approach could bridge gaps in health care services to improve patient care for SCD. CHWs have demonstrated promise in improving health behaviors and outcomes among racial and ethnic minority populations with chronic diseases who lack access to adequate health care [13,14]. CHWs can be integrated into a PCCC team to enhance care coordination and facilitate disease management among adults with SCD. This evidence-based strategy is supported by the Sickle Cell Disease Association of America, a national advocacy organization for the SCD community [15]. Studies have demonstrated that both PCCC and CHW interventions are effective models for supporting disease management in chronic conditions [16,17]. However, there are few models for integrating CHWs into a PCCC team to enhance disease management and patient experiences [17,18]. Furthermore, no published studies have used such an integrative model among African American adults with SCD.

This research will build on our understanding of the role of CHWs in the evidence-based management of SCD and will identify challenges associated with integrating a CHW into a clinical care team. To realize the tenets of this hypothesis, three specific aims will be pursued: (1) assessment of the feasibility of integrating a CHW into a PCCC team for SCD, (2) evaluation of the effectiveness of enhanced care coordination using an integrated PCCC-CHW model on self-care behaviors and patient satisfaction, and (3) determination of the acceptability of the intervention and protocol among patients and care team members through semistructured interviews. Our study will evaluate the hypotheses that by integrating a CHW into a PCCC team, barriers to disease management can be overcome while simultaneously improving the quality of care for adults with SCD.

## Methods

### Overview

The chronic care model (CCM) is a comprehensive framework designed to shift the management of chronic diseases from a reactive approach to a more proactive, planned strategy that emphasizes continuous patient-provider relationships, individualized care, and evidence-based practices across health care systems [19]. It identifies elements of a health care system that encourage high-quality chronic disease care. The CCM posits that productive interactions should occur between patients and providers [19]. However, the framework is limited in describing processes for facilitating these interactions. The proposed study will examine the effectiveness of integrating a CHW as a liaison between patients and providers. This integration is expected to enhance care coordination and support chronic disease management, particularly among adults affected by SCD [13,14].

The theory of self-care management for SCD is adapted from the broader theory of self-care management for vulnerable populations, which describes variables that influence self-care management, health status, and quality of life among populations that experience or are at risk for health disparities [20]. This theory underscores the significance of self-care practices in managing chronic disease, particularly by helping individuals navigate the demands of their condition. In this research, the self-care construct from the theory of self-care management for SCD will be applied as the self-management support element of the CCM, thereby fostering self-care behaviors to improve health outcomes among individuals with SCD.

The goal of this research protocol is to evaluate the feasibility and effectiveness of integrating a CHW into a PCCC team to enhance self-care for adults with SCD. Adopting the CCM and the theory of self-care management for SCD, we hypothesize that a CHW can be successfully integrated into a PCCC team to overcome barriers to disease management and improve the quality of care for adults with SCD (Figure 1).

**Figure 1. F1:**
[figure not shown]
Adapted version of the chronic care model.

Figure 1 illustrates the proposed integrated model. The CCM identifies elements of a health care system that encourage high-quality chronic disease care and emphasizes productive interactions between informed, activated patients and prepared, proactive care teams [19]. For the proposed model, we will assess the effectiveness of a CHW as a liaison to facilitate productive interactions between patients and providers [16-18]. To strengthen theoretical alignment with SCD-specific care needs, the self-management support component of the CCM is operationalized using the theory of self-care management for SCD, which specifies individual-level processes that influence self-care behaviors and health outcomes in this population [20]. Within this integrated framework, CHWs will support self-care skill development, reinforce patient engagement, and facilitate coordination among patients, providers, and community resources. The proposed study will use a CHW to offer social support and implement evidence-based guidelines through virtual or telephone-based sessions. This approach will allow patients to remain in their home setting, where they experience the daily challenges of self-management.

### Ethical Considerations

This protocol will be conducted in accordance with the Declaration of Helsinki. Ethics approval has been granted on an expedited basis by the institutional review board of Georgia Southern University (H21406) for surveys and interviews conducted with human subjects. Informed consent will be obtained from all participants, who will then receive a link to the baseline questionnaire to be completed via Qualtrics XM (Silver Lake and CPP Investments). Each participant will receive a US $20 gift card after completing the questionnaire.

Health Insurance Portability and Accountability Act (HIPAA)–protected information will not be discussed during calls. Information collected during calls will be stored on a cloud server that is only accessible to the research team. To protect the confidentiality of participants, each of them will be assigned a unique participant code.

### CHW Training

In a prior study, the lead investigator conducted a patient-centered outcomes project that trained CHWs on evidence-based management for SCD and the facilitation of education on SCD management for patients and caregivers [21]. On the basis of the study’s findings, we anticipate that participants will perceive CHWs as an acceptable method for delivering SCD education. CHWs (n=2) will be recruited from My Three Sicklers Sickle Cell Foundation Inc (MTS), a Georgia-based community organization that focuses on SCD outreach, management, and policy.

For training, CHWs will complete a “Remote Community Health Worker Certificate” via HomeTown Health, a network of rural hospitals that provides continuing education and training for health care providers. This training provides CHWs with foundational knowledge on the role of CHWs and the delivery of education in remote settings. Once completed, the principal investigator (PI) will provide project onboarding and training for SCD management. MTS will provide ongoing support and supervision of CHWs throughout the study duration.

### Study Design, Setting, and Sample

This study will use a pre-post, nonrandomized, 6-month longitudinal intervention design, implemented using questionnaires and semistructured interviews (Figure 2). Enrollment will occur through the Augusta University Sickle Cell Center’s satellite clinic, Phoebe Putney Cancer Center, in Albany, Georgia. This site has not previously worked with a CHW, either directly or through a community-based organization.

Eligible participants will be adults with SCD aged 18‐45 years. Given the target sample size (n=40), at 80% power and α=.05, we can detect small to moderate effect sizes (*r*^2^=0.4 to 0.6) using a 2-tailed paired *t* test [22]. This sample includes an expected 20% attrition rate. There are currently 97 eligible individuals seeking SCD care at this location. This is more than double the expected enrollment of 30 participants. Using a rolling recruitment process, the PI will work with MTS to enroll additional participants if an enrolled participant is lost to follow-up. The assumption of a small to moderate effect is conservative, given that studies designed to improve self-care in SCD report a medium effect size (*d*=0.71) [8,23].

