This study acknowledges potential limitations, including the feasibility of the sample size, which, while appropriate for evaluating the protocol’s implementation, may limit statistical power to detect significant differences in outcomes. Larger studies using similar protocols would provide concrete data to demonstrate that CHWs are essential contributors to interdisciplinary teams that care for patients with a broad spectrum of chronic diseases. However, the multimethod approach to data collection, incorporating both quantitative measures and qualitative feedback, is a strength that will provide a comprehensive understanding of the intervention’s impact and inform necessary refinements for future research. The focus on adults is particularly relevant given the unique challenges this population faces in accessing consistent and specialized care, especially in areas with geographic disparities [31].

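### The power statement gives r²=0.4–0.6 as a small-to-moderate effect, but on a paired t test that is large; if d=0.4–0.6 was meant, the lower end misses 80% power

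*Protocol article*

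**What the plan says.** The sample size rests on one paragraph of the protocol article, Methods, Study Design, Setting, and Sample. With a target of 40, "at 80% power and α=.05", the authors state that "we can detect small to moderate effect sizes (*r*^2^=0.4 to 0.6) using a 2-tailed paired *t* test". They add: "This sample includes an expected 20% attrition rate". The same paragraph says that participants lost to follow-up may be replaced by further enrollment, and it also gives an expected enrollment of 30.

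The assumed effect is then defended against earlier work: "The assumption of a small to moderate effect is conservative, given that studies designed to improve self-care in SCD report a medium effect size", quoted there as d=0.71. No SD of change and no pre-post correlation is given, and the scale of that d is not stated.

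Data Analysis names the paired t test for the pre-post comparison. Procedures and Data Collection names patient satisfaction and self-care behaviors as the primary outcomes. The Discussion lists as a limitation that the sample size "may limit statistical power to detect significant differences in outcomes".

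**The concern.** The power of a paired t test depends on the mean change relative to the SD of change. An r² can be converted to that scale, but values of 0.4 to 0.6 convert to large effects, so the number and the words attached to it cannot both be right. The more natural guess is that a d of 0.4 to 0.6 was intended. In that case the words roughly fit, but the claimed power has to be checked at the lower end, which is the part that supports the small-to-moderate wording.

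This is the only stated justification of the sample size. Evaluating effectiveness on these outcomes is one of the three aims, and the results are meant to prepare a larger study. A reader who takes the sentence at face value would credit the design with more sensitivity to modest changes than it has.

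**Working it through.** **Inputs.** From Study Design, Setting, and Sample: two-sided α=.05; power 80%; paired t test; target 40; 20% attrition, so 40 × 0.8 = 32 completers if no losses are replaced; up to 40 completers if all are; expected enrollment 30, so 30 × 0.8 = 24 without replacement; effect r²=0.4 to 0.6; reference d=0.71. Assumption: where d is read in place of r², it is dz, because the article gives no pre-post correlation. The alternative is examined in step 4.

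**Formula.** Exact power from the noncentral t distribution with n−1 degrees of freedom and noncentrality dz·√n.

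**1. The plan's figure, taken literally.** From r² = t²/(t² + df) and t = dz·√n, with n=40 and df=39:
- r²=0.4: t² = (0.4/0.6) × 39 = 26.0, t = 5.10, dz = 5.10/√40 = 0.81.
- r²=0.6: t² = (0.6/0.4) × 39 = 58.5, t = 7.65, dz = 7.65/√40 = 1.21.

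Power is above 99% for both values, with 40 and with 32 pairs. About 14 and 8 pairs would be enough for 80%. So 80% is far exceeded, and the stated 80% is not reproduced.

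**2. The range read as dz=0.4 to 0.6, two-sided.**

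| dz | 40 completers | 32 completers |
|---|---|---|
| 0.4 | 69.4% | 59.2% |
| 0.5 | 86.9% | 78.2% |
| 0.6 | 95.9% | 90.8% |

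The upper end holds at both sizes. The lower end fails at both. Reaching 80% at dz=0.4 takes 52 completers, or 52/0.8 = 65 enrolled.

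**3. Smallest dz detectable at 80% power, two-sided.**

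| Completers | Situation | dz |
|---|---|---|
| 40 | 40 enrolled, all losses replaced | 0.45 |
| 32 | 40 enrolled, 20% lost | 0.51 |
| 30 | 30 enrolled, all losses replaced | 0.53 |
| 24 | 30 enrolled, 20% lost | 0.60 |

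Rough check by normal approximation: (1.960 + 0.842)/√40 = 0.44 and (1.960 + 0.842)/√32 = 0.50, slightly below the exact values, as expected.

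**4. Other readings that might rescue the sentence.**
- r rather than r²: r=0.4 gives dz = 0.4/√(1 − 0.16) = 0.44, with power 76.8% (40) and 66.7% (32).
- One-sided α=.05 at dz=0.4: 80.0% with 40 completers, 71.5% with 32. The first matches the stated 80%, but the text specifies two tails. It may be where the figure came from; the article does not say.
- d on the raw-score scale, with dz = d/√(2(1 − ρ)) and ρ the pre-post correlation: d=0.4 reaches 80% if (0.4/0.4543)² = 0.775 ≥ 2(1 − ρ), so ρ ≥ 0.61 with 40 completers. With 32, (0.4/0.5113)² = 0.612, so ρ ≥ 0.69. No ρ is stated.

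**The case against.** The strongest reply is that the power claim does not fail everywhere. Taken literally, r²=0.4 is detected with far more than 80% power. Read as dz, 0.6 is met with 40 and with 32 completers, and 0.5 is met with 40. A raw-score d of 0.4 would be met if the two measurements correlate at about 0.61 or more, which the article neither states nor excludes. All of this stands. A reader might infer that the stated power holds on no reading at all; the document does not support that. What fails is the match between number and label and, on the dz reading, the lower end of the range.

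A reader might also infer that the assumption is plainly not conservative, because 0.81 to 1.21 exceeds 0.71. That follows only if the cited d is on the SD-of-change scale, which the article does not say.

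Nor does the Discussion contradict Methods. It is a hedged limitation, and it can stand beside a stated detectable effect. It does not correct the figure, however.

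Two further points stand. Attrition alone does not settle the number of completers at 32, because replacement could bring it up to 40. And the stated objective is feasibility and acceptability, with results described as preliminary, which limits the harm. Against this, the powered outcomes are named as primary and effectiveness is an explicit aim, so the sentence still needs to be right.

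**Conclusion.** Wrong as written. An r² of 0.4 to 0.6 on a paired t test is a dz of about 0.81 to 1.21, which is large and is also above the cited 0.71 if that figure shares the scale. If dz of 0.4 to 0.6 was intended, two-sided 80% power begins at about 0.45 with 40 completers and 0.51 with 32. Below that the shortfall is material: at 0.4, power is about 11 percentage points under target with 40 completers (69%) and about 21 under with 32 (59%).

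The r² conversion needs no further assumption. The dz figures assume that d would be standardised by the SD of change; on a raw-score scale they shift with the unstated correlation. The range of completers depends on how far losses are replaced and on whether 40 or 30 are enrolled.

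**What to change.** First reconcile the target of 40 with the expected enrollment of 30. Then make these changes:

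1. Delete the r² range and its small-to-moderate label. State instead the smallest standardised mean change (mean change divided by SD of change) that a two-sided paired t test at α=.05 detects with 80% power. If 40 are enrolled: 0.45 with 40 completers (all losses replaced) and 0.51 with 32 (20% attrition, no replacement). If 30 are enrolled: 0.53 with 30 completers and 0.60 with 24.
2. Name the effect-size scale. If a raw-score d is preferred, state the assumed pre-post correlation.
3. Keep the claim that the assumption is conservative only if d=0.71 is confirmed to be on that same scale.
4. Let the limitation in the Discussion cite the restated figure.

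The cost is wording only. If d of 0.4 to 0.6 was meant, the detectable effect becomes slightly less favourable than its lower end. No extra patients are needed and neither the design nor the analysis changes.

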### Procedures and Data Collection

The primary outcomes for this study are patient satisfaction and self-care behaviors (including appointment keeping, tracking health issues, and managing medications). These will be assessed using validated instruments at baseline and after intervention (following the 6-month CHW-integrated PCCC model). Feasibility will be assessed through (1) enrollment numbers within a 2-year time frame, (2) retention, (3) intervention completion, and (4) acceptability of the intervention among participants.

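### Planned enrolment is given as 40 and as 30 in the same paragraph without explanation, and the roughly 35 planned patient interviews fit neither 30 enrolled nor the 32 completers expected from 40

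*Protocol article*

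**What the plan says.** In the protocol article, under Study Design, Setting, and Sample, the power statement reads: "Given the target sample size (n=40), at 80% power and α=.05, we can detect small to moderate effect sizes". The range attached is 0.4 to 0.6, labelled r², for a two-tailed paired t test. The next sentence says: "This sample includes an expected 20% attrition rate". On a plain reading, then, 40 is the number to enrol.

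The same paragraph goes on: "There are currently 97 eligible individuals seeking SCD care at this location". It then adds: "This is more than double the expected enrollment of 30 participants". It also provides for replacing losses; the investigator will work with the community organisation to "enroll additional participants if an enrolled participant is lost to follow-up".

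Two other sections depend on the enrolment number. Procedures and Data Collection says: "Feasibility will be assessed through (1) enrollment numbers within a 2-year time frame", with no figure attached. Study Procedures plans interviews with about 35 patients, invited through the questionnaire given after the final session.

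**The concern.** One design quantity has two values in the current text, and nothing says how 30 relates to 40. This is not detail that a condensed article leaves to a fuller document, because both numbers are stated.

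A reader cannot tell which study the power statement describes: 40 enrolled with 32 completing, or 30 enrolled with fewer completing. The interview plan adds a third number that neither expected count can supply. Feasibility is the study's stated objective and enrolment is the first feasibility measure listed. This paragraph is the only place in the article where a reader can look for the number against which to read it. Enrolment is still open, with 16 enrolled as of March 2026 (Results), so the reference can still be settled before the outcome is known.

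**Working it through.** **Inputs.** From Study Design, Setting, and Sample: target 40, expected enrolment 30, pool 97, attrition 20%, power 80%, two-sided alpha 0.05, paired t test, effect range 0.4 to 0.6, and a comparison effect of d = 0.71 from other studies. From Study Procedures: about 35 patient interviews. From Results: 16 enrolled. Assumption: 0.4 to 0.6 is read as a standardised paired difference d, because r² is not the effect measure of a paired t test.

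**1. The plan's own figure.** Power for n pairs is the probability that a noncentral t variable with n − 1 degrees of freedom and noncentrality d√n falls outside ±t(0.975, n − 1). The number to enrol is n/(1 − 0.2).

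- d = 0.4: 52 pairs; 52/0.8 = 65 enrolled
- d = 0.5: 34 pairs; 34/0.8 = 42.5, so 43 enrolled
- d = 0.6: 24 pairs; 24/0.8 = 30 enrolled

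So 40 does not follow from the lower end of the range. It reaches d = 0.4 only with a one-sided test and no attrition (detectable difference 0.400 with 40 pairs), whereas the text says two-tailed and includes attrition. The figure 30 happens to be the enrolment needed at d = 0.6, but the article does not say that this is its source.

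**2. Can attrition link 40 and 30?**

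- Completers from 40: 40 × 0.8 = 32, which is 2 more than 30.
- Enrolment that yields 30 completers: 30/0.8 = 37.5, so 38, which is 2 fewer than 40.
- Completers from 30 enrolled, without replacement: 30 × 0.8 = 24.

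Neither link is exact, though both are close.

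**3. The pool ratio.** 97/30 = 3.23 and 97/40 = 2.43. Both exceed 2, so the statement is true of either number. The uptake needed is 30/97 = 31% or 40/97 = 41%.

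**4. The interviews.** 35 is more than 30 enrolled and more than 32 completers. To expect 35 completers at 20% loss, enrolment would have to be 35/0.8 = 43.75, so 44.

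**5. What each reading means for power** (two-sided, alpha 0.05).

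| Pairs | How reached | Detectable d at 80% power | Power at 0.4 | Power at 0.6 | Power at 0.71 |
|---|---|---|---|---|---|
| 24 | 30 enrolled, 20% lost, none replaced | 0.597 | 47% | 80% | 92% |
| 30 | 30 enrolled, all losses replaced; or 38 enrolled, 20% lost | 0.529 | 56% | 89% | 96% |
| 32 | 40 enrolled, 20% lost | 0.511 | 59% | 91% | 97% |
| 40 | 40 enrolled, all losses replaced | 0.454 | 69% | 96% | 99% |

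The normal approximation (1.960 + 0.842)/√n gives 0.572, 0.511, 0.495 and 0.443 for the four rows. These are slightly smaller, as expected at these sample sizes.

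**6. Progress.** 16/30 = 53% and 16/40 = 40%.

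**The case against.** The best defence is that 30 is a rounded count of completers that was mislabelled as enrolment. It lies within 2 of the 32 expected from 40, and the detectable difference hardly moves (0.53 against 0.51). This may well be what happened. It would still leave one word wrong, and the interview count would still be too high.

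A second defence is replacement. If losses are made good, 30 enrolled need not shrink to 24 pairs. That stands, and the 24-pair row is therefore conditional on no replacement. But replacement raises the total enrolled, so it cannot explain why expected enrolment is below the target. Full replacement on a base of 40 could supply 35 interviewees; on a base of 30 it could not.

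A third defence is that little power is at stake. At d = 0.71, the only d the article gives, power is at least 92% on every reading. The Discussion also concedes that the sample may limit power. Both points are fair and lower the seriousness.

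Three stronger readings may tempt a reader, and the article does not support them:

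- That the comparison with the 97 eligible patients contradicts 30. It does not: 97 is more than twice both numbers, and at most the phrase sits more naturally with 40.
- That the power statement has no reference. It has one: "Given the target sample size (n=40". What is unsettled is how many pairs will be analysed.
- That the feasibility conclusion turns on which number is used. The article sets no pass mark for enrolment, and one may stand in the full protocol, so no conclusion can be shown to flip.

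**Conclusion.** The inconsistency is real and nothing else in the article resolves it. Planned enrolment is stated as 40 and as 30, a gap of 10 patients or 25% of the target, and about 35 interviews are planned from a group expected to number at most 32 unless losses are replaced.

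Depending on what 30 means, the detectable standardised difference is 0.51, 0.53 or 0.60. The largest value requires both that 30 is truly the enrolment and that losses are not replaced. These figures do not depend on how the printed effect range is read. The conclusion that 0.4 is out of reach (power 47% to 69% across 24 to 40 pairs) does, since it takes 0.4 to 0.6 as a standardised paired difference.

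This should be corrected, but it does not undermine the study. The design is a single-arm feasibility study, the likeliest explanations are benign, and the correction needs no change to conduct.

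**What to change.** State one enrolment number and the number of completers expected from it, and use that pair in all four places: the comparison with the 97 eligible patients, the power statement, the two-year enrolment measure and the interview count. The authors know which number is real; the wording then follows.

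- If 40 is enrolment: give 32 expected completers and a detectable standardised paired difference of about 0.51 (80% power, two-sided alpha 0.05). The pool is 2.4 times enrolment.
- If 30 is the completer count: relabel it, and give enrolment as about 38 and the detectable difference as 0.53.
- If 30 is truly enrolment: restate power as a detectable difference of 0.60 with 24 pairs if losses are not replaced, or 0.53 with 30 pairs if all are. The pool is then 3.2 times enrolment.

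In each case, say whether replacements count towards the enrolment number, bring the interview figure within the expected completers, and restate the lower end of the effect range, since 0.4 read as a standardised difference is not detectable with 80% power at any of these sizes. The cost is wording only.
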